### **13.2 Regulatory status**

The trial is being performed under a Clinical Trial Authorisation (CTA) from the MHRA. This is conditional on all requirements for reporting of adverse events being met, in particular Suspected Unexpected Serious Adverse Reactions (SUSARs). These must be notified by centres to the WCTU who will forward them to the Medicines and Healthcare products Regulatory Agency (MHRA).

### **13.3 Sponsorship and indemnity**

The sponsor of the trial is Velindre NHS Trust as employer of the staff at the Wales Cancer Trials Unit and the Chief Investigator.

#### **Velindre NHS Trust has sponsorship responsibilities as follows:**

- I. Obtaining trial authorisation and appropriate ethics committee opinion – with the following responsibilities delegated to WCTU:
  - Request a Clinical Trial Authorisation (CTA) and subsequent amendments.
  - Selection of Investigators and ensuring each centre has full trial documentation.
  - Ensuring an appropriate ethics committee opinion has been sought and any amendments approved.
  - Giving notice to the MHRA when the trial has ended.
- II. Pharmacovigilance – with the following responsibilities delegated to WCTU:
  - Keeping records of all adverse events reported by Investigators.
  - Ensuring recording and prompt reporting of serious adverse reactions to the CI.
  - Reporting to MHRA and main REC any SUSARs within specified timeframes.
  - Ensuring Investigators informed of SUSARs.
  - Providing annual listing of all SARs to MHRA, Investigators, IDMC and MREC.
- III. Ensuring that the research is conducted in accordance with the principles of Good Clinical Practice (GCP) with the following responsibilities delegated to WCTU:
  - Having quality control systems in place to ensure that the study is conducted according to GCP at all participating centres.

#### **The following responsibilities are delegated to the individual participating centres:**

- Have in place arrangements to adhere to GCP
- Keep a copy of all essential documents (as defined in ICH GCP) and ensure appropriate archiving and destruction once the study has ended
- Take appropriate urgent safety measures.

Non-negligent harm: This trial is an academic, Investigator-led and designed trial, coordinated by the WCTU. The Chief Investigator, local Investigators and coordinating centre do not hold insurance against claims for compensation for injury caused by participation in a clinical trial and they cannot offer any indemnity. The Association of the British Pharmaceutical Industry (ABPI) guidelines will not apply.

Negligent harm: Where studies are carried out in a hospital, the hospital continues to have a duty of care to a patient being treated within the hospital, whether or not the patient is participating in this trial. Velindre NHS Trust does not accept liability for any breach in the other hospital's duty of care, or any negligence on the part of employees of hospitals. This applies whether the hospital is an NHS Trust or not.

### **13.4 Data protection**

The WCTU will act to preserve patient confidentiality and will not disclose or reproduce any information by which patients could be identified (except where patients are registered with the Office for National Statistics or traced via the NHS Central Register, which requires separate consent). Data will be stored in a secure manner and our trials are registered in accordance with the Data Protection Act 1998 and with the Data Protection Officer at Velindre NHS Trust Cardiff.

### **13.5 Publication policy**

Data from all centres will be analysed together and published as soon as possible. Individual participants may not publish data concerning their patients that are directly relevant to questions posed by the trial until the Trial Management Group (TMG) has published its report. The TMG will form the basis of the Writing Committee and advise on the nature of publications.

All publications shall include a list of participants, and if there are named authors, these should include the Chief Investigator, Co-Investigators, Trial Manager, and statistician(s) involved in the trial. If there are no named authors then a writing committee will be identified.

### **13.6 Finance**

SCOPE 1 is funded by the Clinical Trials Advisory and Awards Committee (CTAAC), Funder Number CRUK/07/03, (on behalf of Cancer Research UK, Medical Research Council, and other charities). The trial is in the National Cancer Research Network (NCRN) portfolio and therefore local NCRN support should be available at each participating centre to support entry of patients into this trial.

Cetuximab is manufactured by Merck KGaA who has agreed to supply free cetuximab for all research arm patients for the duration of the protocol treatment.

## 14. QUALITY OF LIFE

Health related quality of life (HRQL) is a secondary outcome for the Phase III part of this trial. The purpose for measuring HRQL in this trial is to assess patients' perceptions of the benefits and harms of treatment that can be subsequently used to fully inform clinical decision-making. In this study it is hypothesised that in the experimental arm there will be fewer patients with recurrent disease and this will lead to better survival. This improved clinical outcome may reflect in HRQL and better scores for physical, role and social function as well as fewer symptoms of fatigue, anorexia and eating difficulties during and following treatment. In patients undergoing the experimental arm it is also hypothesised that the addition of cetuximab to chemoradiotherapy may add additional HRQL problems during treatment (e.g. skin toxicity).

### HRQL aims

- To determine whether cetuximab in addition to chemoradiation improves generic and disease specific aspects of HRQL following treatment than chemoradiation alone. Specific HRQL domains that are expected to be better in the experimental group are: physical and role function, fatigue, dysphagia and eating restrictions
- To determine whether cetuximab in addition to chemoradiation is associated with poorer HRQL during treatment. Specific HRQL domains that are expected to be worse in the experimental arm include: dyspnoea, skin rashes and diarrhoea.

### HRQL instruments

Generic domains of HRQL will be assessed with the EORTC core Quality of Life Questionnaire, the EORTC QLQ-C30^42. This instrument has been well validated in many international clinical trials in oncology including oesophageal adenocarcinoma and squamous cell cancer. The full 30-item measure is composed of multi-item and single scales. These include five functional scales (physical, role, emotional, social and cognitive), three symptom scales (fatigue, nausea and vomiting, and pain), a global health status scale, and six single items (dyspnoea, insomnia, appetite loss, constipation, diarrhoea and financial difficulties). All scales and single items meet the standards for reliability and validity. Disease specific and chemoradiotherapy associated symptoms and side effects will be assessed with the oesophageal cancer specific module, the EORTC QLQ-OES18. This has been validated and tested in patients receiving definitive chemoradiotherapy. It demonstrates good psychometric properties including sensitivity to change over time. The module includes scales assessing dysphagia, eating restrictions, reflux, dry mouth and problems with saliva and deglutition. The Dermatology Life Quality Index (DLQI) will also be administered. This is a well validated, easy to use index which assesses the impact of dermatological conditions on patients' quality of life. It has been included to accurately assess the impact of the acneiform eruption commonly seen with cetuximab. In addition to using the generic and site-specific questionnaires it is proposed to design an additional scale to assess specific symptoms and side effects of cetuximab. At present there are no validated instruments designed for this purpose. During the pilot study, this scale will be developed according to EORTC guidelines for questionnaire development and supervised by [name] in Bristol. It is expected that the final scale will be ready to use within 6 months of the start of the trial.

## **Study design**

This is a multi-centre study and the HRQL evaluation will involve all patients in all participating centres. Patients will be informed in the Patient Information Sheet that they will have their HRQL assessed regularly while involved in the trial.

## **Mode and timing of data collection**

Baseline questionnaires will be given to the patient in clinic after written consent has been obtained and prior to randomisation. Follow-up questionnaires will be completed by the patient during attendance at hospital for clinical visits. Patients will be asked to fill out the questionnaires themselves as completely and accurately as possible. The average time to complete the entire questionnaire is 10-15 minutes. The trials unit will record whether the HRQL forms have been filled in within the specified time window. Reasons for questionnaire non-completion will be recorded. All patients who participate in the SCOPE 1 study will complete questionnaires at all time points.

### **Timing of HRQL assessment**

- Baseline questionnaire.
- During and at end of treatment (Week 7 and week 13).
- Post treatment (24 weeks, time of endoscopy and scan).
- Subsequent follow up will occur at 12, 18, 24 months and annually to 60 months.

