## **Follow up**

- Patients will be seen for clinical surveillance and toxicity assessments three monthly for the first year, four monthly for the second year and yearly for a minimum of five years after treatment, after which follow up should be according to local guidelines.
- Endoscopy and/or CT scan to investigate symptoms suspicious of recurrence as clinically indicated.
- Quality of Life and Health Economics questionnaires annually.

**Primary outcome of stage 1:** Treatment failure rate in the research arm. This will be assessed at 24 weeks (12 weeks after completion of CRT) and is defined as residual disease pathologically confirmed by endoscopic assessment, biopsy and CT scan of thorax and abdomen. The secondary outcome measures are toxicity and feasibility.

**Primary outcome of stage 2:** Overall survival calculated from the date of randomisation to death from any cause. The secondary outcome measures are toxicity, quality of life, quality assurance of radiotherapy and health economics.

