### **5.1 Baseline (pre-treatment)**

Before any study related procedures are undertaken the patient's written informed consent must be obtained. The patient should be given a minimum of 24 hours after the initial invitation to participate before being asked to sign the consent form.

**In addition to the Pre-treatment procedures (4.2) the following are to be carried out prior to treatment. The nurse/doctor will ensure the required data is recorded on the CRFs.**

1. State of Health (EQ-5D) (Appendix VIII).
2. Healthcare Resource Utilisation Log.
3. Blood sample separated and stored or posted fresh (T-SCOPE, translational research, Section 16) (Appendix IX).
4. Dysphagia scale (Appendix X).

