#### **5.4 Follow up**

1. Patients will be seen 3-monthly for the first year, 4 monthly for the second year and yearly for a minimum of 5 years after treatment, after which follow up should be according to local guidelines.
2. Endoscopic assessment and/or CT scans to investigate symptoms suspicious of recurrence as clinically indicated. In the case of local recurrence it will be important to ascertain the relationship of the recurrent disease to the radiotherapy field by comparing endoscopic data at recurrence with the diagnostic/staging endoscopy/EUS and/or CT data with the staging/planning CT scans.
3. Quality of life QLQ-C30 + oesophageal module (QLQ-OES18) + dermatology life quality index (DLQI) (Annually).
4. State of Health (EQ-5D) and Healthcare Resource Utilisation Log (Annually).
- 5. Where recurrence is diagnosed by investigations including endoscopic assessment we request a biopsy sample for translational research.**

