## 5.5 Schedule of Assessments

|                                                                               | Screening     | Cycle 1 |   |                | Cycle 2 |   |                | Cycle 3 |   |                | Cycle 4        |    |                | EOT | Follow up |   |    |    |    |    |    |    |    |  |
|-------------------------------------------------------------------------------|---------------|---------|---|----------------|---------|---|----------------|---------|---|----------------|----------------|----|----------------|-----|-----------|---|----|----|----|----|----|----|----|--|
| Month (Calendar months for study follow up)                                   |               | 1       |   |                |         | 2 |                |         |   | 3              |                |    |                |     | 6         | 9 | 12 | 16 | 20 | 24 | 36 | 48 | 60 |  |
| Week                                                                          | Pre-treatment | 1       | 2 | 3              | 4       | 5 | 6              | 7       | 8 | 9              | 10             | 11 | 12             | 13  | 24        |   |    |    |    |    |    |    |    |  |
|                                                                               |               |         |   |                |         |   |                |         |   |                |                |    |                |     |           |   |    |    |    |    |    |    |    |  |
| Physical History / Exam                                                       | X             | X       |   |                | X       |   |                | X       | X | X              | X H | X  | X              | X   | X         | X | X  | X  | X  | X  | X  | X  | X  |  |
| Height (week 1 only ) & weight                                                | X             | X       |   |                | X       |   |                | X       |   |                | X              |    |                | X   |           |   | X  |    |    |    |    |    |    |  |
| Full blood count                                                              | X             | X       |   |                | X       |   |                | X       | X | X              | X              | X  | X              | X   |           |   |    |    |    |    |    |    |    |  |

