| WHO Performance Status                                                        | X             | X       |   |                | X       |   |                | X       |   |                | X              |    |                | X   | X         | X | X  | X  | X  | X  | X  | X  | X  |  |
| Dysphagia scale                                                               | X             | X       |   |                | X       |   |                | X       |   |                | X              |    |                | X   | X         | X | X  | X  | X  | X  | X  | X  | X  |  |
| Serum renal, liver & bone profile inc. Mg ++                       | X             | X       |   |                | X       |   |                | X       |   |                | X              |    |                | X   |           |   |    |    |    |    |    |    |    |  |
| Electrocardiogram                                                             | X             |         |   |                |         |   |                |         |   |                |                |    |                |     |           |   |    |    |    |    |    |    |    |  |
| Pregnancy test A                                                   | X             |         |   |                |         |   |                |         |   |                |                |    |                |     |           |   |    |    |    |    |    |    |    |  |
| Quality of life QLQ-C30 + oesophageal module + dermatology life quality index | X             |         |   |                |         |   |                | X       |   |                |                |    |                | X   | X         |   | X  |    |    |    | X  | X  | X  |  |
| State of Health (EQ-5D)                                                       | X             |         |   |                |         |   |                | X       |   |                |                |    |                | X   | X         |   | X  |    |    |    | X  | X  | X  |  |
| Healthcare Resource Utilisation Log                                           | X             |         |   |                | X       |   |                | X       |   |                | X              |    |                | X   | X         |   | X  |    |    |    | X  | X  | X  |  |

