#### **Costs and resource utilization**

Costs of cetuximab will be based on discussions with clinicians and finance staff\*, while other healthcare resources utilised by patients during the study period will be collected via the healthcare resource utilisation log administered during treatment and at follow-up. At each of the 3-4 weekly visits, patients will be asked to indicate whether they have had any contacts with their GP, practice nurse, community nurse or attended hospital either as an outpatient or in-patient. They will be asked whether the contact was connected to their condition or for any other purpose. The involvement of others in providing transport and/or support will also be logged. In addition, they will be asked to indicate the medication they have been taking during the 3-4 week period. Consultations with healthcare professionals will be costed using published sources of unit costs and healthcare resources utilised will be added to the respective treatment costs in each arm.

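### Post-treatment questionnaire timing is stated inconsistently, and the Schedule of Assessments leaves month 24 blank for quality of life, EQ-5D and the resource log

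*Protocol*

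**What the plan says.** Four places in the protocol set the timing of questionnaires after week 24.

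- Section 14, Timing of HRQL assessment, covers quality of life only: "Subsequent follow up will occur at 12, 18, 24 months and annually to 60 months".
- Section 5.4 gives quality of life as "Quality of life QLQ-C30 + oesophageal module (QLQ-OES18) + dermatology life quality index (DLQI) (Annually)" and the other two instruments as "State of Health (EQ-5D) and Healthcare Resource Utilisation Log (Annually)".
- The synopsis, under Follow up, agrees with section 5.4: "Quality of Life and Health Economics questionnaires annually".
- The section 5.5 table has follow-up columns for week 24 (month 6) and then months "9 | 12 | 16 | 20 | 24 | 36 | 48 | 60". The row "Quality of life QLQ-C30 + oesophageal module + dermatology life quality index" and the rows for EQ-5D and the resource log are each marked at week 24 and months 12, 36, 48 and 60. Month 24 is blank in all three.

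Two related statements matter. Section 15 describes the resource log thus: "At each of the 3-4 weekly visits, patients will be asked to indicate whether they have had any contacts with their GP", with medication asked about over the same 3-4 week period. Section 5.1 adds EQ-5D to the baseline items with the words "the following are to be carried out prior to treatment", whereas section 4.2 places the QLQ-C30, OES18 and DLQI before randomisation.

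**The concern.** These passages cannot all be followed. Only the protocol is at hand, but a statistical analysis plan could not repair this in any case, because a form that was never handed out cannot be recovered at analysis.

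Two secondary outcomes are affected. Section 14 compares the arms at agreed time points, yet the protocol does not agree on what those are. Section 15 builds QALYs from survival and EQ-5D, and costs partly from the log. Overall survival is powered on the two-year rates, so the month that the table omits is the horizon at which the sample-size calculation states the treatment effect.

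**Working it through.** **1. The schedules side by side (after week 24)**

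| Source | Quality of life | EQ-5D and resource log |
|---|---|---|
| Section 14 | 12, 18, 24, 36, 48, 60 | not covered |
| Section 5.4 and synopsis | 12, 24, 36, 48, 60 | 12, 24, 36, 48, 60 |
| Section 5.5 table | 12, 36, 48, 60 | 12, 36, 48, 60 |

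Quality of life therefore has three versions, and EQ-5D and the log have two. The blank at month 24 does not look like damage in reading the table. Each row has 24 cells that line up with the month header, all three rows agree, and the dysphagia row is marked at month 24, so that visit exists. Month 18 has no column, because the visits fall at months 16 and 20. Section 14 has follow-up questionnaires completed at clinic visits, so month 18 cannot be delivered as written.

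**2. The protocol's survival assumptions**

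Inputs from section 12.3: two-year survival 35% (control) and 47.5% (research), HR 0.71, 80% power, two-sided 5%, 3 years of recruitment plus 1 year of follow-up, 420 patients, 269 events. Allocation is 1:1. The exponential shape and uniform accrual are my assumptions.

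- Hazards per year: λ = −ln S(2)/2, which gives 0.525 and 0.372. The ratio of logs, ln 0.475 / ln 0.35, is 0.709.
- Required events: 266 (Schoenfeld) or 271 (Freedman) at HR 0.709; 268 or 273 at HR 0.71. The stated 269 is reproduced.
- Event probability: 1 − [e^(−λ) − e^(−4λ)]/(3λ) = 0.702 and 0.585, mean 0.643. Then 420 × 0.643 = 270 events, which also agrees.

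**3. Who dies between months 12 and 36**

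| | Control | Research |
|---|---|---|
| S(12 months) | 0.592 | 0.689 |
| S(24 months) | 0.350 | 0.475 |
| S(36 months) | 0.207 | 0.327 |
| Die in months 12-36: S(12) − S(36) | 0.385 | 0.362 |
| As a share of those alive at month 12: 1 − S(36)/S(12) | 0.650 | 0.525 |

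Pooled, (0.385 + 0.362)/2 = 0.373, or about 157 of 420 patients. Deaths before month 12 are similar: (0.408 + 0.311)/2 = 0.360, about 151 of 420.

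**4. What a month-24 form would add**

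- Share of month-12 survivors alive to complete it: S(24)/S(12) = 0.59 and 0.69.
- Share of those who die in the gap who would still be alive at month 24: [S(24) − S(36)]/[S(12) − S(36)] = 0.143/0.385 = 0.37 and 0.148/0.362 = 0.41.
- Patients alive at month 24: (0.35 + 0.475)/2 × 420 = about 173.
- Longest scheduled gap: 24 months under the table, 12 months with month 24 added.

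At the analysis time assumed in section 12.3, about one third of patients were randomised 36 months or more earlier. Under the table, about two thirds would have month 12 as their last scheduled questionnaire; with month 24 this falls to about one third.

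**5. Sensitivity**

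With the 51% two-year survival of the UK series in section 2.2, deaths in months 12-36 are 0.51^0.5 − 0.51^1.5 = 0.714 − 0.364 = 0.35. The conclusion does not change.

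**6. Log recall and baseline EQ-5D**

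On treatment, section 5.2 and the table give the log at weeks 4, 7, 10 and 13, which fits a 3-4 week recall. After week 13 the table's next logs are at week 24, month 12 and month 36, so no visits run at the interval that section 15 describes. For baseline EQ-5D, section 6.1 has treatment starting within two weeks after randomisation, and section 1.2 describes the trial as open. A form due only before treatment may therefore be completed after the allocation is known.

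**The case against.** The strongest reply is that the text outvotes the table. The synopsis, section 5.4 and section 14 all include month 24, and only the table lacks it. This stands in part: loss of month 24 is a risk, not an established fact. But section 5 introduces its tables as the follow-up schedule, so a site could reasonably work from them. That sites do so is inference.

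Several stronger readings are tempting, and the documents do not support them.

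- A reader might infer that the gap falls when most patients die. About 37% of all patients die in it, roughly as many as before month 12. It is a majority only of those alive at month 12.
- A reader might infer that QALYs are unobserved over this period. Survival is followed throughout, and EQ-5D is scheduled up to month 12 and again from month 36. What is missing is any scheduled utility measurement between them.
- A reader might infer that post-treatment costs go largely unrecorded, by applying a four-week recall to the follow-up logs. The protocol ties that recall to the 3-4 weekly visits and states no window for later logs. Section 15 also names the patient diary, and section 12.2 names CRF data and resource data from finance and clinical staff.
- A reader might infer that baseline EQ-5D is planned after randomisation. The table puts it in the same pre-treatment column as the QLQ-C30, and the synopsis lists the two together. The section 5.1 wording permits late completion but does not plan it.

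These are secondary outcomes, and nothing here affects the primary survival comparison.

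**Conclusion.** The contradiction is real and should be removed. Quality-of-life timing has three incompatible versions, EQ-5D and the log have two, and month 18 has no visit. If sites follow the table, no quality-of-life, utility or resource form is scheduled between months 12 and 36. About 37% of all patients are expected to die in that period, including 65% of control and 53% of research patients alive at month 12.

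These percentages rest on exponential survival through the protocol's two-year rates, which reproduces its stated events. They ignore the interval of up to two weeks between randomisation and the start of treatment. The completion shares for a month-24 form are upper limits, since not every surviving patient returns one. The log recall and baseline EQ-5D points are smaller matters of wording, and no effect on the results has been quantified for either.

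**What to change.** - Reconcile sections 5.4, 5.5 and 14, and the synopsis where needed, to one schedule. Mark month 24 for quality of life, EQ-5D and the log in the section 5.5 table.
- Delete month 18 from section 14, or move it to an existing visit (month 16 or 20).
- Keep the on-treatment logs at weeks 4, 7, 10 and 13.
- State in section 15 that each follow-up log covers the period since the last log.
- List baseline EQ-5D with the pre-randomisation questionnaires in section 4.2.

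The cost is wording and table edits, plus one extra set of forms at a visit that patients already attend (at most about 173 patients under the planning assumptions). The follow-up log would also ask for recall over a longer period, which is less accurate than 3-4 weeks. Moving EQ-5D to the pre-randomisation list needs no new visit.

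### The protocol gives three conflicting follow-up schedules for the questionnaires, and the 5.5 table leaves month 24 blank for the quality-of-life forms, EQ-5D and resource log

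*Protocol*

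**What the plan says.** Four places in the protocol set the timing of follow-up questionnaires.

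- **Section 14, Timing of HRQL assessment.** After the week-24 form, "Subsequent follow up will occur at 12, 18, 24 months and annually to 60 months". The instruments are the QLQ-C30, OES18 and DLQI. On how they are collected, the same section says: "Follow-up questionnaires will be completed by the patient during attendance at hospital for clinical visits".
- **Section 5.4, Follow up.** Visits are described as "Patients will be seen 3-monthly for the first year, 4 monthly for the second year and yearly for a minimum of 5 years after treatment". The QLQ-C30/OES18/DLQI, and separately the EQ-5D and resource log, are each listed as annual.
- **Synopsis, Follow up.** The quality-of-life and health-economics questionnaires are annual.
- **Section 5.5, Schedule of Assessments.** After month 6 the follow-up columns run "9 | 12 | 16 | 20 | 24 | 36 | 48 | 60". The row "Quality of life QLQ-C30 + oesophageal module + dermatology life quality index" is marked at months 12, 36, 48 and 60. The EQ-5D row and the row "Healthcare Resource Utilisation Log" carry the same follow-up marks. All three are blank at months 16, 20 and 24.

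Section 5 opens by directing the reader to the tables for the follow-up schedule.

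**The concern.** These are instructions on what to hand to a patient at a given visit, and they disagree. A site following section 5.4 collects at month 24. A site following the table does not. A site following section 14 also looks for an 18-month visit that neither section 5.4 nor the table provides.

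Three uses of the data are affected. Section 14 plans to compare the arms at individual time points and in a repeated-measures model, yet the protocol does not settle what those points are after month 12. It also says that all patients complete forms at every time point and that the trials unit records whether forms arrive within their window. Compliance cannot be judged against three different lists. Section 15 builds QALYs from follow-up EQ-5D scores and costs from the resource log. Under the table, both would have to be carried across the two years from month 12 to month 36.

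An analysis plan cannot repair this, because a form that was never given out cannot be recovered.

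**Working it through.** **1. Is the blank at month 24 real?** Each table row was split at its column separators and every mark was matched to its month or week header. The month header, the week header and the rows checked (quality of life, EQ-5D, resource log, dysphagia scale, physical examination, endoscopy) all have 25 cells, so the columns line up. Known entries confirm this:

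- endoscopy falls at pre-treatment and week 24 only;
- physical examination falls at every follow-up month, including 24;
- the quality-of-life row falls at pre-treatment and weeks 7, 13 and 24, as sections 4.2, 5.2 and 5.3 require.

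The blank is therefore unlikely to come from reading the PDF. Physical examination, performance status, dysphagia scale and toxicity are all marked at month 24, so a visit does take place.

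**2. The schedules side by side (months after the week-24 form).**

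| Source | Quality-of-life forms | EQ-5D | Resource log |
|---|---|---|---|
| Section 14 | 12, 18, 24, 36, 48, 60 | not scheduled there | not scheduled there |
| Section 5.4 and synopsis | 12, 24, 36, 48, 60 | 12, 24, 36, 48, 60 | 12, 24, 36, 48, 60 |
| Section 5.5 table | 12, 36, 48, 60 | 12, 36, 48, 60 | 12, 36, 48, 60 |

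Four-monthly visits in year 2 fall at months 16, 20 and 24. The 18-month form therefore has no scheduled visit. Under the table, the gap between consecutive forms is 36 − 12 = 24 months.

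**3. Size of the gap.** The protocol gives no figure for this, so an illustration is needed. Inputs from section 12.3: two-year survival of 35% (control) and 47.5% (research), and 210 patients per arm. Assumption: exponential survival, so the number alive at month t is 210 × S(24)^(t/24).

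| Month | Control | Research | Total |
|---|---|---|---|
| 12 | 210 × 0.35^0.5 = 124 | 210 × 0.475^0.5 = 145 | 269 |
| 24 | 210 × 0.35 = 73.5 | 210 × 0.475 = 99.75 | 173 |
| 36 | 210 × 0.35^1.5 = 43 | 210 × 0.475^1.5 = 69 | 112 |

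If every site followed the table, about 173 patients alive at month 24 would not be given each form. Of those alive at month 12, 1 − 0.35 = 65% of controls and 1 − 0.475 = 52.5% of the research arm would die before month 36. Under the table, their month-12 form would be their last.

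**The case against.** The strongest reply is that the table is outnumbered. Section 5.4, the synopsis and (for quality of life) section 14 all call for month 24. The trials unit sends out the CRFs and questionnaires (section 4.3), checks forms for timeliness and compliance (10.2) and sends reminders for overdue data (10.4). Nothing shows that sites would follow the table alone. This stands: the loss is conditional, and 173 is an upper bound. It does not remove the defect, because section 5 points readers to the table and checks on timeliness need one agreed list.

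A reader might infer more than the documents support, in four ways:

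- **Month-18 forms as an added loss.** The EQ-5D and resource log were never planned at month 18. For the quality-of-life forms, the 18-month point appears only in section 14, has no visit, and may reasonably be dropped. Only month 24 should be counted.
- **Month 24 as a key quality-of-life time because survival is planned on two-year rates.** Those rates express the hazard ratio of 0.71 for a log-rank test. They do not make month 24 an analysis time for quality of life, which is a secondary outcome without its own sample size.
- **Bias between the arms.** Allocation is minimised by centre (section 4.3), so a site's choice of schedule should affect both arms about equally. The main cost is precision.
- **No information at all in the gap.** The dysphagia scale is marked at months 16, 20 and 24. The gap concerns the quality-of-life questionnaires, EQ-5D and resource log.

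**Conclusion.** The contradiction holds. The synopsis and section 5.4, the section 5.5 table, and section 14 give three different follow-up lists for the questionnaires. The table omits month 24 for all three rows although the visit exists, and section 14 names a month with no visit. A site that relied on the table would have a 24-month gap in quality-of-life, EQ-5D and resource data.

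The loss is at most about 173 month-24 forms per instrument. That rests on full accrual of 210 per arm, the protocol's two-year survival rates being met in both arms, exponential survival, every site following the table, and complete return of forms otherwise. The actual loss would be smaller if some sites followed section 5.4.

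The primary outcomes are untouched, and the assessments up to month 12 agree across the sections. The point is modest, but it should be corrected because the missing forms cannot be recovered later.

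**What to change.** In the section 5.5 table, mark month 24 in the row for the QLQ-C30, OES18 and DLQI, in the EQ-5D row and in the Healthcare Resource Utilisation Log row. Section 5.4 and the synopsis already require this for all three, and section 14 requires it for the quality-of-life forms. In section 14, either delete the 18-month assessment or move it to an existing visit (month 16 or 20) and mark that visit in the table. The synopsis and sections 5.4, 5.5 and 14 should then be read together to confirm that they give one list.

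The cost is a correction to the table and the CRF pack. For patients it adds a questionnaire that section 14 puts at 10-15 minutes, with the EQ-5D and resource log, at a visit that already takes place.
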